### Fidelity of pamphlet

The fidelity of the teaching materials and pamphlet have been established by a panel of experts including three experienced registered nurses, one dietitian and two nutritionists. All of them have more than 10 years of experience in their own areas of expertise. A checklist was completed by each expert. The checklist indicates all components and aspects of the intervention that the participants will receive, from precontemplation to action stages. Self-report measures of consistency will be in binomial (yes/no) and ordinal (1 = Not relevant, 2 = Somewhat relevant, 3 = Quite relevant, 4 = Highly relevant) formats in multiple item surveys. The advantages of using this method are the low cost, ease of administration and speed of data collection. All experts agreed that the proposed teaching materials should include HPI items with stage-based TTM given through WhatsApp. However, one of the experts did not agree with the others on the content of one item. All the items related to goals, processes, strategies and HPI were rated either “Quite relevant” or “Highly relevant”.

### Development of questionnaire

A questionnaire (Additional file 3) has been developed on the basis of several studies [26, 27, 107–110]. This consists of six study aspects: (1) Personal information; (2) Working characteristics; (3) Eating habits; (4) Health promotion programme for healthy eating; (5) Stage of change; and (6) Decisional balance and self-efficacy.

The questionnaire includes 11 items to assess the Hong Kong firefighters’ eating habits, especially their fruit and vegetable consumption. These questions are based on a series of eating habit studies [26, 27, 107, 108]. The consumption of fruit and vegetables will be measured by asking: (1) “How often did you consume fruits/vegetables in the past week?” (responses ranging from “Not consumed” to “Seven days”); (2) “Where do you usually have fruits/vegetables?” (three choices are “At home”, “During duty” or “No difference, at home and during duty”); and (3) “On a day you consumed the fruits/vegetables, how much did you take on average on that day?” (in bowls or servings). For eating habits, the questions also included “On average, how many days do you have breakfast/lunch/dinner/night snack (take away included) within a week?” (responses ranging from “None” to “More than 5 days”) and “How about the speed of having meals when you are on duty in the fire station when compared to the meals you eat at home?” (responses ranging from “Slower” to “Faster”).

Thirty-five questions were designed to understand decisional balance. Based on Ma et al. (2003) [110], they address the pros, cons and self-efficacy of eating fruit and vegetables. The decisional balance will be evaluated by asking the participants how important each of the pros and cons is in their decisions to consume recommended amounts of fruit or vegetables, using 5-point Likert scales ranging from 0 (Not at all important) to 5 (Very important). Eight pros and nine cons for fruit intake and eight pros and ten cons for vegetable intake will be used to assess the decisional balance.

Twelve questions were designed to assess self-efficacy by rating, on 5-point Likert scales ranging from 0 (Very difficult) to 5 (Very easy), how difficult or easy the participants find it to eat based on the recommendations in six high-risk situations, for each of the two dietary habits [109].

Four questions were designed to identify the stages of change in eating fruit and vegetables (i.e. “How many servings of fruits/vegetables the respondent usually consumed each day; intention to eat ≥ 2 servings a day of fruit or ≥ 3 or more servings a day of vegetables; whether the participant had been consuming ≥ 2 servings of fruit or ≥ 3 servings of vegetables for more than 6 months; intention to eat more). The participants will then be asked to state their intentions to have servings of fruit and vegetables by choosing one of five statements, each representing a stage of change: “No, and I do not intend to in the next 6 months” [Precontemplation]; “No, but I intend to in the next 6 months” [Contemplation]; “No, but I intend to in the next 30 days” [Preparation]; “Yes, I have been doing so for less than 6 months [Action]; Yes, I have been doing so for more than 6 months [Maintenance]. These four questions and their related intentions were drawn from De Vet et al. (2006) [109].

Another three questions were developed to assess the Hong Kong firefighters’ points of view about the healthy eating promotion: (1) “Can a healthy eating promotion programme help you to change or understand your eating attitudes and habits?”; (2) “Can a pamphlet on healthy eating alone facilitate you to change or understand your eating attitudes and habits?”; (3) “Can a healthy eating promotion programme delivered through a mobile app facilitate you to change or understand your eating attitudes and habits?” The firefighters will be required to rate these three questions on 4-point Likert scales ranging from 1 “Absolutely cannot” to 4 “Absolutely can”.

### Validity of questionnaire

A panel of six experts, three nursing professionals, one dietitian and two nutritionists was invited to establish the content validity for the questionnaire. The content validity index (CVI) was 0.966, with average item CVIs ranging from 0.667 to 1.000 and individual panel members’ CVIs ranging from 0.885 to 0.987. These results indicate that the questionnaire is valid to investigate the firefighters’ eating habits. The original English version of the questionnaire was translated into Chinese by a professional translator, and another professional translator performed back-translation, obtaining a CVI of no less than 0.8. The reliability of this questionnaire was examined using test-retest reliability. Ten firefighters from the HKFSD, who fulfilled the inclusion criteria for the study, were invited to take part in this reliability test. Their healthy eating habits was examined on day 1 and day 15 (2 weeks in between) using this questionnaire. The agreement between the data collected on these 2 days ranged from 0.704 to 1.00, with a mean of 0.75. All of these correlation coefficients were significant at the 0.01 level.

### Body measurements

Anthropometric data will be the secondary outcome of this study (Additional file 4). The participants will be weighed wearing light clothing and no shoes. Body weight will be measured by the researcher using an Innocare weighting scale. When measuring body height, a Butterfly Brand measuring tape and a 10-in. triangular ruler will be placed perpendicular to the wall to mark the top of the participant’s head, and a Butterfly Brand measuring tape will then be used to measure the distance along the wall from the floor to the ruler. The BMI (in kilograms/meters squared) will be calculated from height and weight measurements. Waist circumference and hip circumference will be measured by the researcher, using the Butterfly Brand measuring tape.

In order to ensure the reliability of the data collected by the researcher, a professional nurse will be invited to perform the data collection alongside the researcher to ensure inter-rater and intra-rater reliability. The measurement will be performed by the researcher and the professional nurse. The agreements between the professional nurse and the researcher should keep the intraclass correlation coefficient (ICC) at no less than 0.8 [111–113] for each measurement.

### Randomization

The participating firefighters who fulfil the inclusion criteria are stratified into different clusters on the basis of the location of their fire stations prior to the randomization process. These clusters will be randomly assigned to be either intervention or control groups by using a simple randomization method which involves a set of random numbers generated by a computer. Odd and even numbers will represent the control and intervention groups respectively. In order to minimize the bias in this randomization, this process will be conducted by an information technology (IT) expert who is independent of the research team and has more than 15 years’ experience in this field. Furthermore, this IT expert will be blinded during this process. All the participants will be blinded as well, which means they will not know whether they are in the intervention or control groups.

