**Methods:**

This will be a cluster randomized control trial study. The participants will be assigned randomly into either control (health promotion pamphlet) or intervention (health promotion pamphlet and education materials through WhatsApp) groups. Changes in healthy eating habits will be assessed by a self-administered questionnaire and anthropometric measurements at three different time points.

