## Methods/design

### Study design

A two-armed, pre-post test, clustered randomized control trial (CRCT) design will be used in this study. Figure 1 shows the overall design. The data will be collected at three time points: T_0_, baseline; T_1_, 3 months after the completion of an 8-week intervention; and T_2_, 6 months after the intervention.

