### Participants

The participants, firefighting teams’ members from the Hong Kong Fire Service Department (HKFSD), will be recruited from fire stations during their free time by the distribution of promotional pamphlets to firefighters in their corresponding fire stations through their fire station colleagues. When a potential participant expresses his interest to participate in this study, he will receive a detailed information sheet (Additional file 1), consent form (Additional file 2) and baseline questionnaire (Additional file 3). Each fire station will be treated as an individual cluster.

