### Recruitment

The participants will be recruited from more than one fire station, located in different districts in Hong Kong. Convenience and snowball sampling methods will be used for the recruitment. The associated participants will be assigned randomly into either intervention or control groups. All the associated participants will be blinded to their intervention allocation.

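### Unrestricted odd/even randomisation of fire stations guarantees no balance; with few stations an arm can be left empty or with a single station

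*Protocol article*

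**What the plan says.** The Study design section declares a cluster trial: "A two-armed, pre-post test, clustered randomized control trial (CRCT) design will be used in this study". The Participants section defines the cluster: "Each fire station will be treated as an individual cluster". The Randomization section gives the allocation rule, "These clusters will be randomly assigned to be either intervention or control groups by using a simple randomization method", and how the numbers are used: "Odd and even numbers will represent the control and intervention groups respectively".

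The same section says that firefighters "are stratified into different clusters on the basis of the location of their fire stations prior to the randomization process". In context this describes sorting men into their stations. It sets up no strata within which stations are balanced, and the section names no block, pairing, fixed ratio or minimum per arm.

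On the number of clusters, the text shown has only this, under Recruitment: "The participants will be recruited from more than one fire station, located in different districts in Hong Kong". Two places speak of allocating participants instead of stations: the Abstract ("The participants will be assigned randomly into either control (health promotion pamphlet) or intervention") and Recruitment ("The associated participants will be assigned randomly into either intervention or control groups").

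**The concern.** Simple randomisation works well for many units, because large imbalances are then rare. Here the units are fire stations, and a planned sample of 38 firefighters suggests few of them. Separate odd/even draws for a handful of stations often give lopsided arms and can leave an arm with one station or none.

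An empty arm leaves no comparison. With one station in each arm, no analysis can separate the intervention from whatever else differs between the two stations. With one station in one arm and several in the other, variation between stations can be estimated from one side only, and the comparison rests on an assumption about the single station.

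Station effects are plausible on the protocol's own account. The Background says that firefighters eat together on shift, that peers shape eating, and that this influence has to be controlled. Research questions 1 to 3 under Study aims are all comparisons between the arms.

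**Working it through.** **Inputs.** The cluster is the fire station (Participants). Allocation is simple, odd to control and even to intervention (Randomization). The number of stations, k, is more than one (Recruitment) and otherwise not given in the text shown. Two assumptions are added: each station's draw is independent with probability 0.5 for each arm, and k takes the values tabulated. The plan states no balance figure of its own to reproduce.

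**Formulas.**
- All stations in one arm: 2 × 0.5^k.
- Some arm has at most one station: (2 + 2k)/2^k for k of 4 or more. The 2 counts the two empty-arm outcomes and the 2k counts the outcomes with exactly one station in an arm. For k = 2 or 3 the probability is 1, since every split leaves an arm with one station or none.

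**Results under the stated rule.**

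| k | All in one arm | Some arm has 0 or 1 station |
|---|---|---|
| 2 | 2/4 = 50% | 100% |
| 4 | 2/16 = 12.5% | 10/16 = 62.5% |
| 6 | 2/64 = 3.1% | 14/64 = 21.9% |
| 8 | 2/256 = 0.8% | 18/256 = 7.0% |
| 10 | 2/1024 = 0.2% | 22/1024 = 2.1% |

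With k = 2, the half of outcomes that do not leave an arm empty put exactly one station in each arm.

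**Results under a restricted draw.** If half the stations go to each arm, the first column is 0 for every k of 2 or more. The second column falls from 62.5% to 0 at k = 4 (2:2) and from 21.9% to 0 at k = 6 (3:3). With k = 2 or 3 a restricted draw prevents an empty arm but still leaves an arm with one station, so four stations is the smallest number that allows two per arm.

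**What a single station per arm does to the planned test.** The Data analysis section names t tests and chi-square tests between groups, at a significance level of 0.01. Take one station of 19 men per arm (38/2) and an intraclass correlation ρ. The true variance of the difference in means is 2[ρ + (1 − ρ)/19]. The unadjusted test works with 2(1 − ρ)/19. The ratio of the two is 1 + 19ρ/(1 − ρ), which is 1.19, 2.00 and 3.11 for ρ = 0.01, 0.05 and 0.10. Dividing the critical value of t on 36 degrees of freedom by the square root of that ratio gives a true type I error of about 0.018, 0.062 and 0.132, against the nominal 0.01. The values of ρ are assumptions. The document gives none for the outcomes, and the ICC under Body measurements concerns agreement between raters.

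**The case against.** The strongest reply is that k is unknown. The phrase about more than one station describes where men will be recruited and need not be a design minimum. The article condenses a fuller protocol, and the study design figure is not shown; either could give the count. At eight stations an empty arm has a probability of 0.8%, and at ten 0.2%. This stands: the size of the risk depends on k, and the absence of the count from an article is not itself a fault. It does not rescue the rule, which is stated and guarantees no balance at any k.

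A second reply is that the main purpose is feasibility, and adherence and retention can be estimated without balanced arms. That is true, but the article also poses three between-arm questions and cites power to detect an effect size.

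Three stronger readings are tempting and are not supported:

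- A reader might infer that the trial did run with two stations, or that its comparison is invalid. Nothing in the document shows how many stations took part or how they were split.
- A reader might take the participant wording in the Abstract and Recruitment as a real conflict over the unit of allocation. In a trial that declares itself cluster randomised and defines the station as the cluster, it is largely shorthand and needs only a wording edit.
- A reader might charge the rule with a large loss of efficiency even when both arms are filled. Averaging 4a(k − a)/k², where a is the number of stations in one arm, over all splits with no empty arm gives 0.86 to 0.88 for k = 4 to 8. That average counts one-station arms as usable. Requiring two stations per arm gives 1.00, 0.93 and 0.91 for k = 4, 6 and 8, with equal station sizes assumed.

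**Conclusion.** The point holds as a weakness in a stated rule. Odd/even allocation of stations offers no protection against an empty or single-station arm, and a free alternative does. The risk is serious for about six stations or fewer: a 21.9% chance of an arm with at most one station at six, and 62.5% at four. It is modest at eight (7.0%) and small at ten (2.1%). These figures rest on independent draws with probability 0.5 and on assumed values of k. The document does not establish that the trial was in fact compromised, and it supports no minimum beyond the four stations needed for two per arm.

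**What to change.** **The rule.** Replace simple randomisation with restricted allocation. Once the participating stations are known, the independent IT expert draws at random from the allocations that place half the stations in each arm (as near half as possible if the number is odd). Stations may be paired on size or district first. Require at least four stations, so that each arm has at least two.

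**This trial.** The Trial status section records recruitment as closed on 30 October 2019 and completion on 29 February 2020, so the allocation can no longer be changed. Report the number of stations and of participants in each arm, and make no between-arm inference if either arm has a single station. Use restricted allocation in the later cluster trial that this study is meant to inform.

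**Wording.** As a minor edit, align the Abstract and Recruitment sentences with station-level allocation.

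**Cost.** The restricted draw is free. It needs the list of stations to be complete before allocation. If fewer than four stations would otherwise have taken part, more must be approached for the same number of men; 38 men over four stations is 9.5 per station. Reporting the counts per arm costs one line in the results.

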#### Intervention group

The participants in the intervention group will be required to complete the questionnaire, and their anthropometric data will be recorded. Then they will receive the pamphlet from the researcher at T_0_ and the baseline stage-matched teaching material every 2 weeks through WhatsApp.

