#### Control group

Similarly, the participants in the control group will also be required to complete the questionnaire, and their anthropometric data will be recorded. The only difference between the intervention and control groups is that the participants in the control group will receive the pamphlet (the same as for the intervention group) from the researcher at T_0_ only.

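### Participants are stated to be blinded to their group, but only one arm receives WhatsApp lessons and the primary outcome is self-reported

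*Protocol article*

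**What the plan says.** The protocol article claims participant blinding twice. Under Recruitment: "All the associated participants will be blinded to their intervention allocation". Under Randomization the term is defined: "All the participants will be blinded as well, which means they will not know whether they are in the intervention or control groups".

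The arms are described under Data collection. Intervention participants get the pamphlet at T0 and then "the baseline stage-matched teaching material every 2 weeks through WhatsApp". For the other arm, "the participants in the control group will receive the pamphlet (the same as for the intervention group) from the researcher at" T0 only, and the Control group section presents this as the sole difference between the groups. Study design gives the intervention a length of 8 weeks, with follow-up 3 and 6 months after it ends.

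Study aims names changed eating habits as the primary outcome, with BMI and waist-to-hip ratio as secondary. The Abstract says that eating habits are assessed by a self-administered questionnaire. Data analysis states that the statistician is blind to group.

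**The concern.** The contrast between the arms is something a participant sees on his own phone. A design of that kind cannot deliver participant blinding unless the control arm receives something comparable, and nothing comparable is described.

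For an outcome that the participant does not influence by reporting, the wording would be a minor slip. Here the participant is the outcome assessor. The lessons promote fruit and vegetables, and the questionnaire then asks on how many days, and in what amounts, he ate them. A man who knows he has been taught may report more than he eats. If that shift is larger in the taught arm, the between-arm difference moves towards benefit with no change in diet. A reader told that participants were blinded would have reason to discount that explanation, and would be wrong to do so.

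**Working it through.** No stated figure is at issue, so there is none to reproduce. The check sets the sections side by side.

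1. **What is claimed.** Randomization does not leave blinding undefined. It says participants will not know which group they are in, and Recruitment repeats the claim without qualification.

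2. **What each arm receives.**
   - Pamphlet at T0: both arms, same content.
   - Teaching material by WhatsApp: intervention arm only. With one delivery every 2 weeks over 8 weeks, 8 / 2 = 4 deliveries, or 5 if one is also sent on day 0. Control: 0.
   - Sham or attention messages for control: none described.

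3. **Whether anything else hides the arm.**
   - The reminder not to disclose information (Inclusion criteria) is aimed at contamination. It does not hide a participant's own materials from him.
   - Allocation by fire station separates the arms physically but has no bearing on what a participant sees himself receive.
   - WhatsApp reminders 1 month and 2 days ahead (Data collection) go to participants generally, but they announce follow-up visits and carry no teaching content.

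4. **Consequence for the statement.** A participant who receives the lessons knows that he is being taught beyond the pamphlet. The sentence in Randomization therefore cannot hold for the intervention arm. For the control arm it depends on what participants are told about the other arm, which the documents do not show.

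5. **Consequence for the outcome.** Write the observed between-arm difference in change as the true difference plus (reporting shift in intervention minus reporting shift in control). Over-reporting that is constant from T0 onwards cancels in the change, and a shift common to both arms cancels in the difference. Only a shift that is larger in the taught arm remains. Blinding is what would make the two shifts equal in expectation, and it is absent. The documents give no value for either shift, so the term cannot be computed.

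**The case against.** The strongest defence is that participants may not know what the other arm receives. The information sheet is not shown. Control participants get an active pamphlet with the same content as the teaching material, stations are separate, and participants are asked not to share what they receive. A control participant might well not know that he is the control. This stands as far as it goes. It would support a claim that the other arm's content is concealed, but the protocol makes a different and stronger claim, that participants do not know their own group.

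It can also be said that the outcome is measured 3 and 6 months after the lessons end, by which time any reporting effect may have faded, and that the study is exploratory and claims only potential effects. Both are fair. They limit how much bias to expect; they do not make the blinding statement true.

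A reader might infer more than the documents support:

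- *That the measurer is unblinded.* The sections say "Waist circumference and hip circumference will be measured by the researcher", and the researcher also hands out the pamphlets. But the pamphlet is the same in both arms, so handing it out reveals nothing, and no section says who sends the WhatsApp material.
- *That the baseline questionnaire discloses the arms.* One item asks "Can a healthy eating promotion programme delivered through a mobile app facilitate you to change or understand your eating attitudes and habits" and another asks about a pamphlet alone. These are general opinion items. They do not name WhatsApp, do not say that the formats are being compared, and do not say which one the respondent will get.
- *That the information sheet reveals the design.* It covers aims and procedure, but its text is not available.
- *That the outcome itself is described as blinded.* The protocol applies the word to participants, and states openly that the questionnaire is self-administered.

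**Conclusion.** The statement of participant blinding is wrong as written and should be corrected. The finding rests on the article's own sections: a defined claim of blinding, visibly different treatment of the arms, and no sham contact for control. It is certain for the intervention arm and undetermined for the control arm.

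The effect on the primary outcome is a possibility with a plausible direction, towards the intervention. Its size is unknown. A figure in standard deviations could be set against the planning effect size of 0.6, but it would be a bare assumption, so none is offered. The secondary outcomes are measured rather than self-reported and so are less exposed. No finding is made about masking of the person who measures them.

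**What to change.** - In Recruitment and Randomization, withdraw the statements that participants are blinded. Describe them as unblinded or, if something is in fact concealed, say exactly what, for example the content of the other arm.
- Among participants and those analysing the data, claim blinding for the statistician only, as Data analysis already states.
- Word the primary conclusion as an effect on self-reported eating habits, including fruit and vegetable intake, in unblinded participants. State that reporting bias in favour of the intervention cannot be excluded.

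The cost is a few sentences. Trial status reports recruitment closed on 30 October 2019 and completion on 29 February 2020. The correction therefore belongs in the protocol record, in the report of results and in the plan for the larger trial.

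Two further changes might suggest themselves and are not recommended. Moving the opinion items off the baseline form comes too late, and would achieve little once participants are described as unblinded. Masking the nurse is doubtful: measurement may take place at the fire stations, which are the units allocated, and although "a professional nurse will be invited to perform the data collection alongside the researcher", the nurse is not said to measure every participant at every time point.
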